# A geographical cluster randomised stepped wedge study of continuing medical education and cancer diagnosis in general practice

**DOI:** 10.1186/s13012-014-0159-z

**Published:** 2014-11-07

**Keywords:** Denmark, General Practice, Continuing Medical Education, Diagnosis, Early Detection of Cancer, Barriers

## Abstract

**Background:**

Denmark has inferior cancer survival rates compared with many European countries. The main reason for this is suggested to be late diagnosis at advanced cancer stages. Cancer diagnostic work-up begins in general practice in 85% of all cancer cases. Thus, general practitioners (GPs) play a key role in the diagnostic process. The latest Danish Cancer Plan included continuing medical education (CME) on early cancer diagnosis in general practice to improve early diagnosis. This dual aims of this protocol are, first, to describe the conceptualisation, operationalisation and implementation of the CME and, second, to describe the study design and outcomes chosen to evaluate the effects of the CME.

**Methods/Design:**

The intervention is a CME in early cancer diagnosis targeting individual GPs. It was developed by a step-wise approach. Barriers for early cancer diagnosis at GP level were identified systematically and analysed using the behaviour system involving capability, opportunity and motivation described by Michie et al. The study will be designed as a geographical cluster randomised stepped wedge study. The study population counts 836 GPs from 417 general practices in the Central Denmark Region, geographically divided into eight clusters. GPs from each cluster will be invited to a CME meeting at a certain date three weeks apart. The primary outcomes will be primary care interval and GP referral rate on cancer suspicion. Data will be obtained from national registries, GP-completed forms on patients referred to cancer fast-track pathways and GP-completed online questionnaires before and after the intervention.

**Discussion:**

To our knowledge, this will be the first study to measure the effect of a theory-based CME in early cancer diagnosis at three levels: GP knowledge and attitude, GP activity and patient outcomes. The achieved knowledge will contribute to the understanding of whether and how general practice’s ability to perform cancer diagnosis may be improved.

**Trial registration:**

Registered as NCT02069470 on ClinicalTrials.gov.

**Electronic supplementary material:**

The online version of this article (doi:10.1186/s13012-014-0159-z) contains supplementary material, which is available to authorized users.

## Background

Denmark lags behind many European countries in cancer survival. It has been suggested that late diagnosis and more advanced cancer stage at treatment lie at the root of this problem [1-9]. In order to minimise the time from referral to diagnosis, some countries have implemented fast-track pathways for cancer, e.g. the 2-week wait in the United Kingdom and the cancer pathways in Denmark [10,11]. Such organisational initiatives are largely dependent on the prevailing referral patterns in general practice. Selecting patients for referral for suspected cancer is a complex procedure which is influenced by 1) the general practitioner’s (GP’s) personal characteristics such as knowledge, skills, clinical judgement, risk-taking disposition and attitude; 2) organisational factors such as access to tests and investigations; and 3) patient-related factors such as expectations, symptom presentation and communication-style preferences. It is by no means a straightforward task to set the bar for referral [12]. Over-investigation has clinical and financial consequences, whereas under-investigation may delay diagnosis and have medico-legal implications.

The key role of general practice in earlier cancer diagnosis is indisputable; 85% of Danish cancer patients presented symptoms to general practitioners on their route to diagnosis [13]. Previous studies have found that cancer patients had an increased number of visits to general practitioners 6 months prior to diagnosis [14] and that 25% of all cancer patients had a primary care interval of more than 20 days until referral according to the GPs [15,16]. Thus, there seems to be a potential for earlier referral and possibly also for earlier diagnosis [17-21]. However, as the average Danish GP sees only eight to ten new cancer patients per year, cancer is a relatively rare disease in primary care. Half of the diagnosed cancer patients are known to present with what the GPs report as alarm symptoms, while the other half tend to present with non-specific or vague symptoms [13,15]. When patients present cancer-related symptoms to general practitioners, their probability of having cancer is low because even alarm symptoms of cancer have low positive predictive values (PPVs; below 5%) [22-30]. Yet, the proportion of cancer patients among patients referred to cancer fast-track pathways is high (PPVs of 10%–30%) [31,32], which implies that the GPs may somehow introduce a higher threshold for referral.

To improve cancer diagnostics in Denmark, the latest Danish Cancer Plan included continuing medical education (CME) targeting GPs as a key strategy to optimise cancer symptom recognition among GPs and to facilitate referral to fast-track pathways. The CME initiative provided an important opportunity to measure if and how targeted CME may influence the participating GPs’ knowledge, attitude and activity in the context of referral for cancer suspicion.

The primary aim of this article is to describe the conceptualisation, operationalisation and implementation of CME to enhance cancer diagnostics in primary care. A second aim is to describe the study design and outcomes chosen to evaluate the effects of the CME.

## Method

### The CME intervention

#### Setting

The study was performed in one of the five Danish Regions (Central Denmark Region) which has 1.27 million inhabitants and 417 GP clinics with 836 GPs. In Denmark, GPs own their private clinics and are on a contract with the Danish Regions on a central, negotiated scheme [33]. Part of this scheme includes remuneration for participation in CME. As a first line in the Danish healthcare system, the GPs provide free access to medical advice and act as gatekeepers to hospital and private specialists. Each citizen (99%) is listed with a specific general practice clinic.

The regional CME on early cancer diagnosis was initiated by a team comprising researchers, a regional academic coordinator, hospital-GP liaison advisors, a CME supervisor and three leading hospital consultants. A working group was established to operationalise the CME. This group counted four academic GPs of whom two were hospital-GP liaison advisors, one CME supervisor and one researcher ([name]). A research group (the authors) identified the barriers as described below. The Danish government funded the CME.

#### Identification of barriers at GP level for early cancer diagnosis

The key aim of the CME was to optimise cancer-related referral from general practice clinic to hospital in an attempt to identify underlying cancers at an earlier and more amenable stage. The target for the intervention was the individual GP, and the CME was developed in a stepwise manner as described by Grol et al. [34]. Initially, the research group identified barriers at the GP level for early referral using a number of methods: input from research literature, brainstorm among the four GPs in the working group, individual GP interviews made by the first author ([name]), a focus group interview with six GPs [35], experiences from audit of lung cancer diagnosis in general practice in the UK [36], and Danish GPs’ responses to the Module 3 International Cancer Benchmarking Partnership (ICBP) questionnaire [37]. The barriers identified through this process were shared with the members of the working group, and they were included in the CME if considered both important and possible to change (Figure 1).

**Figure 1 Fig1:**
[figure not shown]
**The process of identifying the important barriers to be included in the CME program.**

One barrier was “Insufficient GP knowledge about the positive predictive values (PPV) of cancer symptoms”. This barrier signifies that GPs have not acquired full knowledge of the PPVs based on primary care populations [22-27,38]. It was hypothesised that this could prevent GPs from knowing what would be the PPV upon referral of patients to the fast-track cancer pathway (below 10%). Another barrier was “Lack of recognition of the ‘low-risk-but-not-no-risk’ symptoms”. This barrier reveals the absence of awareness of non-specific, vague symptoms [39,40]. “Lack of knowledge on benefits of early diagnosis” suggests an insufficient understanding of the fact that 2–4 weeks’ delay in diagnosis may cause stage progression for some cancers [41] and that waiting time in general can have an impact on prognosis [8,42]. Another important issue, “false reassurance from a normal test and other pitfalls”, covers the fact that GPs felt reassurance when an ordered test turned out normal or was used on mistaken indications. This reassurance could arise because of the false negative nature of the results (e.g. chest x-ray missing 15-20% of lung cancers [43]) or because a negative test result was used to exclude a cancer diagnosis (e.g. normal blood counts). Awareness of typical pitfalls [44] in early cancer diagnosis was thus considered important to the GP’s choice and interpretation of a test.

“High risk-taking” indicates the existence of a high GP referral threshold [45]. The threshold is considered to be too high since the observed proportion of cancer patients in Danish fast-track pathways (typically 10-30%) [31,32] is higher than the PPVs of alarm symptoms. “Low use of fast-track pathway referral for cancer suspicion” indicates that in some situations GPs refer patient to an ordinary hospital investigation rather than to the more optimal cancer fast-track pathway. This could be explained by an incomplete implementation or a concern for overuse of the fast-track referral option. “Inadequate experience with online cancer guidelines” indicates a need for more experience in the use of the regional website for referral. It was hypothesised that such a website would heighten the GPs’ knowledge about referral criteria and receiving departments and that the presence of this website would allow the GPs an opportunity to better inform the patient about the investigation and overall reduce time spent. “Difficulties in communicating cancer risk” concealed an uncertainty in how to communicate risk to a patient. This item was evaluated as important since, opposite ordinary referral, referral to a fast-track pathway required that the GP informed the patient about their suspicion of cancer. Thus, some GPs did not refer patients to cancer fast-track investigation as they did not want to worry the patient.

#### Addressing the identified barriers and developing the CME elements

According to the theoretical frame described by Michie et al. [46], any changes in the GP’s clinical behaviour (B) will be governed by their psychological and physical capability (C), social opportunity (O) and motivation (M) to change. Using this COM-B-model, the identified barriers were analysed, and the elements of the CME were subsequently developed (Table 1).

**Table 1 Tab1:** **The operationalisation of the specific CME elements based on the identified barriers**

**Barriers**	**Capability Psychological/physical**	**Opportunity Social** **/physical**	**Motivation Automatic** **/reflective**
Insufficient GP knowledge of PPV of symptoms of cancer	Positive predictive values for cancer symptoms.	PPV cards followed by explanation were delivered as hand-outs to bring home to practice.	
Lack of recognition of the “low risk but not no risk” symptoms	Only 50% of cancer patients presented organ alarm symptoms.		Evoking emotions by watching the educational film. Case-based experience. Exchanging experience from daily practice.
Lack of knowledge of benefits of early diagnosis	Explaining the waiting paradox. Delay may influence prognosis.		Understanding the value of early diagnosis.
False reassurance from a normal test and other pitfalls	20% of lung chest X-rays are false negative. Only 33% of ovarian tumours can be found with a gynaecological examination. Blood test cannot exclude a risk of cancer.		
High risk-taking	Cancer is a low-prevalence condition in general practice. Even alarm symptoms have low PPVs for cancer. This explains the need for having a low PPV for cancer among referred patients.	Debate on pros and cons of early cancer diagnosis. Opinion leaders and hospital consultants backing up earlier referral.	Understanding the need for having a low PPV for cancer among referred patients. Debate on cost and overdiagnosis. Debate on the GP’s role
Low use of fast-track cancer pathway referral	Fast-track referrals reduce diagnostic intervals. If not, it is a challenge for the hospital to redirect patients referred via the usual route to a cancer fast-track pathway or the patient risks investigatory delay.	Fast-track pathways for cancer investigation already available. Increasing experience in using regional GP website raised awareness on referral guidelines.	Sharing experience. Accepting that 95% of referred patient will not have cancer.
Inadequate experience with online cancer guidelines	Reintroducing the regional GP homepage. Guiding in search strategy and contents, including referral guidelines.		Improving the GP’s self-confidence in decision-taking
Difficulties in communicating cancer risk	Most patients presenting alarm symptoms had been worried about cancer before consulting a general practitioner.	Patient leaflets were delivered to support communication about cancer risk.	Sharing experience on cancer risk communication.

The CME-elements were approached by capability, opportunity or motivation (COM).

The psychological capability is the GP’s ability to engage in the necessary thought processes related to comprehension and reasoning. The cognitive part of the CME would increase the GP’s knowledge about the PPVs of cancer symptoms and increase his or her awareness of the identified pitfalls in cancer diagnosis. This was believed to lead the GP to perform a more correct cancer risk assessment and thereby optimise referral procedures. The CME would point out that referral-delay could worsen the prognosis to dispel the myth that cancer develops over several years and that another month therefore would not change the prognosis [8,47].

The physical capability covers the skills necessary to perform concrete manoeuvres. The CME reintroduced how to access the regional website and shortly described the contents and search tool. Furthermore, the communication skills about cancer were addressed through case-based discussion on how and when to inform a patient about cancer risk.

The GPs’ physical opportunity to refer patients suspected of having cancer exists through the already established fast-track pathways and existing guidelines. The CME included no intervention in this area. The social opportunity was indirectly addressed by including a local opinion leader and a local hospital consultant in the team of lecturers to emphasise that a change of attitude towards lowering the referral threshold is widely recommended.

Motivation includes the reflective processes involving evaluation. Risk taking was addressed through case-based discussion and by raising questions about what it implies to be a competent GP. Motivation also comprised automatic processes involving emotions and impulses arising from associative learning. To address these processes, the CME included an educational film developed to illustrate a GP’s handling of a patient with a complex medical history. By identifying with the GP actor and by subsequently discussing his struggle and lack of readiness to do the definitive investigation, it was intended that the GPs would store this experience in their mind for later pattern recognition.

#### Form of CME

The CME took place as a 3-hour session. According to the available evidence, the teaching approach was multifaceted, partly didactic, but mostly interactive [48,49]. The key points were first explained and illustrated by an oral presentation, next they were discussed in a reflective debate based on two clinical patient scenarios and one educational film to create a scenario similar to that encountered in clinical practice and decision-making. Hands-on models of tumours were placed in the lecture room. PPV diagrams on lung, colorectal, ovarian and prostate cancer [22-27] were printed in hard copy as a clinical tool. Furthermore, leaflets for specific fast-track pathway to support communication about risk of cancer were offered in a plastic retainer, also to bring home to the clinic. The CME schedule is shown in Table 2.

**Table 2 Tab2:** **The schedule for the 3-hour CME meeting provided in the eight clusters**

**Time (minutes)**	**Form**	**Lecturer**	**Barriers**	**Content**
10	Introduction	Regional academic coordinator		Presentation of schedule and lecturer
10	Plenary discussion	Hospital-GP liaison advisors, GP participants	Risk-taking, PPVs of symptoms	Questions regarding risk-taking and symptoms PPVs
10	Reflection, group discussion	GP participants	Risk-taking	
			PPVs of symptoms	
25	Power point presentation	Primary care researcher	Benefits of early diagnosis	GP role in cancer diagnosis, times to diagnosis matter
	Plenary discussion		Risk-taking	Early stage—vague symptoms
			Use of fast-track referral	Description of use of fast-track referral contra usual referral
10	Power point presentation	Hospital-GP liaison advisors	Use of fast-track referral	Audit on quality of referral letters and discharge letters in relation to cancer investigation
10	Power point presentation	Senior doctor from local hospital	Risk-taking	Cancer diagnosis at hospital level
	Plenary discussion		Use of fast-track referral	Cooperation with primary care
			Communicating risk	Always inform patients about cancer suspicion
10	Group discussion	GP participants		Debate: How are diagnostics done in your clinic?
10-min break (hands-on models were introduced)				
40	Educational film	Hospital-GP liaison advisors	Risk-taking	Educational film discussed in sequences
	Group discussion	GP participants	Use of fast-track referral	Awareness of barriers, pitfalls and difficulties in an everyday general practice setting.
	Plenary discussion		“Low risk but not no risk”	
			False reassurance/pitfalls	
			Communicating risk	
40-min break—dinner				
45	Power point presentation	Primary care researcher	PPVs of symptoms	Cancer patients’ symptoms in general practice
	Patient cases	Hospital-GP liaison advisors	“Low risk but not no risk”	Debate on patient cases
	PPV diagram		Risk-taking	Demonstration of use of PPV diagrams (handouts)
			False reassurance/pitfalls	
10	Power point presentation	Hospital-GP liaison advisors	Online cancer guidelines	Reintroduction of regional GP homepage.
			Communicating risk	Leaflets to support communicating cancer risk

#### Lecturers

The CME sessions were conducted by a team of six persons with different healthcare backgrounds. They consisted of an academic primary care researcher to increase the new evidence-based knowledge; two hospital-GP liaison advisors to reduce the gap between research knowledge and everyday life in practice; a local CME supervisor to establish a safe atmosphere and to facilitate acceptance of the knowledge by being considered a local opinion leader; a local hospital consultant to guarantee that the proposed changes could be anchored locally and to ensure a debate of any local issues that could act as barriers to the implementation. A regional academic coordinator introduced the program and ensured that time was kept.

#### Lecture room

The CME was intended to reach as many GPs as possible in the Central Denmark Region. Geographical accessibility was therefore important, and the CME sessions were accordingly arranged as eight local meetings. The meeting rooms had high-quality audio-visual equipment and were laid out with round tables for 6–8 people. Participants were offered catering during the meeting, and a friendly, relaxed atmosphere was established.

#### Piloting

A full-scale CME session was conducted with the Regional Cancer Steering group as audience. Feedback from the session was used to further adapt the CME.

### Study design

The effect of the CME intervention will be evaluated in a geographical cluster randomised stepped wedge design [50]. All GPs in the Central Denmark Region were allocated to one of eight clusters based on their clinics’ geographical location. CME was offered as a 3-hour meeting to each cluster with 3 weeks’ interval in between clusters. Clusters with delayed intervention will serve as controls for clusters that have already received interventions (Figure 2).

**Figure 2 Fig2:**
[figure not shown]
**The stepped wedge design to evaluate the effect of the CME.** The first time point to the left indicates the baseline measurement where all of the clusters were controls (C). At subsequent time points, clusters received the CME intervention and crossed over to interventions (I). All clusters eventually received the intervention. The bottom of the figure focuses on one cluster to illustrate the data collection and the three subgroups for stratification: 1) GPs who participated in the CME; 2) GPs who did not participate in the CME, but who had at least one colleague who participated; 3) GPs who did not participate in the CME and who had no colleagues who participated.

The Regional Cancer Care Unit generated the random allocation sequence which was based on the pragmatic principle that dates for CME should be applicable for that geographical area (taking into account other arrangements in the area, the availability of venue, etc.). The same independent administrative unit enrolled and assigned clusters to the CME. The researchers were not involved in the randomisation. The GPs were not aware of the interventional design. The main researcher was present at the meeting, but only to register participants and to observe that the CME was delivered as planned to evaluate uniformity. She could not interfere with the participants or the CME conduct.

#### Study population and recruitment of GPs to the CME

All GPs from the Central Denmark Region were invited to the CME. The CME was announced in each cluster by mail invitations 2 months before and again 1 month before the CME. Additionally, the description of the meeting was available on the regional GP website. Each GP willing to participate in the CME was registered at sign-up and again upon arrival at the CME.

#### Inclusion and exclusion criteria for patients

Included are all patients referred from general practice to the fast-track pathway for cancer except patients suspected for non-melanoma skin cancer. Excluded are patients already diagnosed with cancer within five years prior to the date of referral.

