### Outcomes

#### The primary outcomes

Primary care interval is defined as the time from the first presentation of a cancer-relevant symptom in primary care until the date of referral to secondary care for investigation [16]. It was hypothesised that the CME would lower the primary care interval by increasing the GP’s readiness to refer.GP referral rate is defined as the number of patients referred by a specific GP to a cancer fast-track pathway per 1000 patients listed with the GP. The CME was expected to increase the referral rate.

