#### The secondary outcomes

GP knowledge is defined as knowledge on *i)* Cancer as a condition with a low prevalence, *ii)* PPVs for cancer of selected symptoms, *iii)* Typical pitfalls and *iii)* Initial cancer presentation. This is measured by requesting the GP to indicate a probability percentage (0-100%) on questions such as; *what is the likelihood of a 50-year-old patient having cancer at the time you choose to refer to a cancer fast-track pathway? What is the likelihood of a patient, smoker, aged 40 and above, having lung cancer the second time the patient presents with haemoptysis in your practice? What is the risk for a lung cancer not being detected on a chest x-ray at the time of diagnosis?* W*hat is the proportion of patients with colorectal cancer who initial presented an alarm symptom*?GP attitude towards early cancer diagnosis, assessed as a score on a 1–5 Likert scale. It is defined as attitude to *i)* Use of fast-track referral, i.e. whether the referral option is considered complicated and/or time-consuming. *ii)* Use of healthcare resources, i.e. whether risk taking is affected by fear of overuse or fear of delayed diagnosis. *iii)* Use of patient resources, i.e. whether risk taking is affected by fear for unnecessary distress or need for necessary investigation to find those with cancer in an early stage.GP self-assessed readiness to refer is defined as the proportion of hypothetical patients referred at their first presentation based on GP responses to patient scenarios (vignettes) concerning cancer diagnosis. 4) GP-assessed risk of cancer for referred patients. 5) Referred patients’ GP visit rates 6 months prior to diagnosis compared with their earlier use of general practice. 6) The proportion of patients with cancer among referred patients for each GP (GP’s PPV for diagnosing cancer when a patient is referred to the cancer fast-track pathway). 7) Cancer patients’ clinical tumour stage at the time of initiating treatment. 8) Cancer patients’ one-year survival measured as the proportion of cancer patients per GP alive one year after the date of diagnosis (Figure 3).

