#### One-page forms on referred patients: Development, pilot testing, and data collection

This form was used to collect specific clinical information on patients referred from GPs to the fast-track pathway on cancer suspicion. The one-page form requested the patient’s personal identification number, the date of hospital referral, the date of first presentation of symptoms in general practice related to cancer suspicion, the symptoms presented at the time of referral, the specific fast-track pathway, and the GP’s assessment of the patient’s risk of cancer. GPs were asked to rate a specific risk for cancer by indicating a probability percentage (0–100) (Additional file 2).

All the items mentioned above have previously been validated in studies performed by the Research Unit [15,44]. The form was piloted in three steps. Seven GP trainees were observed while they filled in the form about the most recent patient they had referred on cancer suspicion. They were interviewed about any problems encountered and how they understood the items. Three GPs then completed forms in their daily practice over a 2-week period in order to check its feasibility. Finally, 21 GPs were asked to fill out and subsequently send the forms electronically to the Research Unit to verify the feasibility of the electronic transfer and the optical scanning of the forms [51].

In August 2012, all GPs in the Central Denmark Region received a pad with 25 forms. They were requested to complete a form each time they referred a patient to a cancer fast-track pathway within an 8-month period (September 2012-May 2013). Patients referred to fast track were also identified in a regional database (PAS) and in a radiological database (breast cancer). If the GP form was missing, the GP was sent a form for the particular patient and kindly requested to complete it. This form was extended with an item on the patient’s route into a fast-track pathway investigation to include only patients referred from GPs on cancer suspicion (Additional file 3).

The one-page form was designed and processed in the computer programme Teleform Enterprise Version 8.0 (Cardiff software Inc., San Marcos, CA, USA). Handwritten data including presenting symptoms were coded by the first author ([name]) before scanning [51].

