#### Register data

Each inhabitant with a permanent residence in Denmark has a 10-digit personal identification number, the CPR number. This number is registered in the Danish Civil Registration System and allows linkage between all national registries at the individual level. A cancer patient’s vital status will be obtained 12 months after the date of diagnosis.

The provider number registry contains the names and addresses of every Danish GP, the number of GPs in each general practice, and patient list size including the patients’ sex and age.

The Primary Care Referral Registry (an online database) stores copies of all electronic referral letters sent from general practice to hospital. We will develop an algorithm to identify patients referred on cancer suspicion in the 8-month study period to increase the completeness of the data on referred patients.

The Danish National Patient Registry [52] will be used to obtain information about comorbidity and cancer diagnoses.

The Danish National Health Service Registry [53] will be used to count the number of contacts of referred patients to general practice during the 6 months preceding the referral date. Each patients previous use of general practice patient will be counted and serve as a basis for comparison.

The Danish Cancer Registry [54] will be used to identify patients with cancer among all referred patients. From this registry, we will also obtain data on date of diagnosis, cancer type and tumour stage.

Statistics Denmark [55] holds data stored in the Integrated Database for Labour Market Research. These data will be used to calculate a deprivation score for each general practice (Table 3).

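### Interval, stage and one-year survival are compared among fast-track referrals, a group the CME is meant to change, so patient mix alone can bias them in either direction

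*Protocol article*

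**What the plan says.** All places are in the protocol article.

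- **Population** (Inclusion and exclusion criteria for patients). The analysed group is set as: "Included are all patients referred from general practice to the fast-track pathway for cancer except patients suspected for non-melanoma skin cancer". Patients with a cancer diagnosis in the five years before referral are excluded.
- **Interval data** (One-page forms on referred patients): "This form was used to collect specific clinical information on patients referred from GPs to the fast-track pathway on cancer suspicion".
- **Cancer cases and stage** (Register data): "The Danish Cancer Registry [54] will be used to identify patients with cancer among all referred patients", followed by "From this registry, we will also obtain data on date of diagnosis, cancer type and tumour stage".
- **Stage and survival as outcomes** (The secondary outcomes, items 7 and 8): both refer simply to cancer patients, and survival is "measured as the proportion of cancer patients per GP alive one year after the date of diagnosis". The restriction to referred patients is not repeated there. It comes from the two sections above.
- **Expected effect on entry to the group** (The primary outcomes): "The CME was expected to increase the referral rate". The referral rate is itself a primary outcome.
- **How the CME should act** (Identification of barriers at GP level, and Table 1): one targeted barrier is that "in some situations GPs refer patient to an ordinary hospital investigation rather than to the more optimal cancer fast-track pathway". Others are failure to recognise vague, low-risk symptoms and too high a referral threshold. GPs are taught that a low proportion of cancers among those they refer is desirable.
- **Biases discussed** (Strengths and limitations of the study): selection among the three GP subgroups, information bias from forms completed on request, and lead time for survival. A change in which patients enter the analysis is not mentioned.

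**The concern.** Clusters are randomised to CME dates, and that protects comparisons between everyone listed with the practices before and after the CME. It does not protect a comparison restricted to people who have passed through a gate that the CME itself moves. After the CME, the fast-track group should contain patients who would otherwise have been referred by the ordinary route, later, or not at all. If their intervals, stage or prognosis differ from those of patients who would have been fast-tracked anyway, the phases differ even though no patient's course has improved.

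At stake are one primary outcome and two patient outcomes. An apparently shorter interval could reflect added patients with short intervals. A real improvement could be hidden by rerouted patients with long ones. The other primary outcome, referrals per 1,000 listed patients, is not exposed to this problem because its denominator is the patient list.

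**Working it through.** **1. The plan's own figures (Power calculation).** Comparing 25% with 20%, two-sided alpha 0.05, 99% power, pooled variance and no continuity correction gives 2,558 per arm, 5,116 in total, as stated. Iterating the stepped wedge design effect with k = 8, b = t = 1 and an intra-cluster correlation of 0.05 gives DE = 0.3231 and a total of 1,653, as stated. Expected forms: 2,200 / 0.20 × 0.70 = 7,700, as stated. The point is therefore not an arithmetic error.

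**2. Effect of mix on the interval.** Suppose no existing fast-track patient's interval changes. Let f be the relative growth in fast-track referrals and q the share of added patients with an interval over 20 days. Then

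p_after = (0.25 + f × q) / (1 + f).

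The 25% is the plan's design value. The Background reports it for cancer patients, whereas the forms cover all referrals. The documents give neither f nor q, so the values below are assumptions.

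| f | q | calculation | share over 20 days |
|---|---|---|---|
| 0.20 | 0.13 | (0.25 + 0.026) / 1.20 | 23.0% |
| 0.20 | 0.25 | (0.25 + 0.050) / 1.20 | 25.0% |
| 0.20 | 0.35 | (0.25 + 0.070) / 1.20 | 26.7% |
| 0.20 | 0.40 | (0.25 + 0.080) / 1.20 | 27.5% |
| 0.25 | 0 | 0.25 / 1.25 | 20.0% |
| 0.50 | 0.10 | (0.25 + 0.050) / 1.50 | 20.0% |

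The shift is zero when q equals the existing 25%, negative below that and positive above it.

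**3. Effect of routing on survival.** The Power calculation expects 2,200 of 5,400 cancers (41%; the assumed share is 40%) to come through the fast track. Assume one-year survival of 80% in those cancers and a rise in the captured share from 40% to 50% of all cancers:

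- newcomers survive at 50%: (0.40 × 0.80 + 0.10 × 0.50) / 0.50 = 74%;
- newcomers survive at 90%: (0.40 × 0.80 + 0.10 × 0.90) / 0.50 = 82%.

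No patient's outcome differs between the two lines. The survival figures are assumptions too. Stage is exposed in the same way.

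**4. Would a list-based rate settle the interval question?** It fixes the denominator, but the numerator still counts only fast-track referrals. Take 100 referrals, 25 of them long. Let the CME truly cut the 25 to 20 and add 20 patients, 7 of them long (35%). There are then 27 long intervals against the same patient list, so the rate of long intervals rises despite a real improvement. The crude share is 27 / 120 = 22.5%.

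**The case against.** **Certainty and size.** A reader might infer that the comparison is biased, in a known direction and by a known amount. The documents do not support that. Growth and mix are unknown, the illustrations run both ways, and the bias is zero if added patients resemble existing ones. A reader might also take 23.0% for the plan's diluted target, since 5 percentage points × 40% participation = 2 points. The Power calculation says the effect is reduced for participation but never gives 23%, and its sample size reproduces from 25% against 20%. The 2-point target is one reading of an unclear paragraph. This objection stands and limits the claim to what can happen.

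**Signals already in the design.** The referral rate, GP-assessed risk and the proportion of cancers among referred patients would show a change in mix. Symptoms, pathway and comorbidity are collected, covariate adjustment is foreseen, and its details may properly sit in an analysis plan. This stands in part. Those outcomes reveal a shift without correcting it, and adjustment among referred patients cannot bring in cancers diagnosed by other routes.

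**Stage and survival population.** Outcomes 7 and 8 do not themselves say referred patients only. That is correct, but the inclusion criteria and the described registry search point to the restricted reading. The planned Primary Care Referral Registry algorithm aims to find more of the referred patients and does not redefine the group.

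**Dilution.** An all-cancer analysis includes many patients whom the CME could hardly reach. That stands and is a reason to add this analysis alongside the fast-track one.

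**Conclusion.** The concern holds as a risk of selection bias of unknown size and direction. The plan assesses the interval, and on the natural reading also stage and survival, in a group defined by a post-intervention event that the CME is designed to enlarge and change, and the article does not discuss this. Under plausible but assumed inputs, mix alone moves the over-20-day share from 25% to anywhere between 20.0% and 27.5%. The lower end equals the full effect the study was sized for. The documents do not show that such a shift will occur. The referral rate per 1,000 listed patients and the stated sample sizes are unaffected. The change should be made: it is cheap, and Trial status says that register data had not yet been obtained.

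**What to change.** **(a) Stage and one-year survival.** Alongside the fast-track analysis, analyse all incident cancers among persons listed with the 417 practices, by linking the cancer registry to the patient lists through the CPR number.

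- Keep the exclusions for non-melanoma skin cancer and prior cancer. The five-year window now runs back from referral, so it needs an anchor date that exists for every cancer.
- Fix in advance the date that assigns a cancer to the control or intervention phase. With 3-week steps, using the diagnosis date places some cancers referred before the CME in the intervention phase.
- State in The secondary outcomes which population each of items 7 and 8 uses.

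**(b) Interval.** Report, as supporting analyses for reading the crude proportion:

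- the rates of fast-track referrals with intervals over 20 days and of 20 days or less, each per 1,000 listed patients;
- the proportion over 20 days standardised to the control-phase mix of age, sex, pathway and symptoms.

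Do not make a fall in the rate of long intervals a condition for claiming shorter intervals. As the working shows, rerouting can raise that rate despite a true improvement.

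**Cost.** Extra analysis on registers already named, and possibly a wider data permission. The all-cancer analysis covers about 5,400 cancers against about 2,200, but its effect is diluted: about 60% of cancers are expected outside the fast-track route, 15% do not start in general practice, and only 40% of GPs are expected to attend. These figures overlap and should not be multiplied. The larger count should not be presented as a gain in power without a calculation.
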